### Outcomes

We will evaluate the IUDPs’ effects in relation to three entangled key dimensions: residents’ health, social equity, and ecological sustainability. To capture the complexity of change processes, we distinguish between different analytical levels, reflecting short- to long-term developments: “Outputs” refers to directly observable, short-term changes in the neighbourhood’s physical and social environment (e.g. new infrastructure, renovated public spaces), “Outcomes I” relates to early behavioural changes and modifications in local structural conditions, “Outcomes II” addresses medium-term effects on socio-ecological sustainability, such as increased participation or improved environmental quality, and “Impacts” describes long-term effects and more fundamental changes at the level of the broader societal system and overall context, such as strengthened resilience or reduced inequalities. To support this evaluation framework, we have developed a generic logic model applicable to all three IUDPs illustrating these levels and their interconnections (see Fig. 3).

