#### Social equity

Regarding social equity, we will examine different aspects of environmental justice, namely distributional and procedural justice [37]. Distributional justice will be operationalised by analysing social disparities in exposure to environmental stressors as well as access to resources. Using survey data, we will compare living and housing conditions across different population groups, stratified by various socioeconomic factors such as income, education, migration experience, and employment status. Additionally, survey data will be used to analyse which social groups will be affected – positively or negatively – by potential changes resulting from the IUDP interventions.

To assess procedural justice, we will explore participants’ involvement in environmental and political decision-making. We will distinguish between three aspects: their knowledge of opportunities to participate in decision-making processes, their intention to engage – such as by signing a petition, attending an information event, or submitting a complaint to local authorities – and their actual past participation.

We will also use the Short Scale Measuring Perceived Social Participation to capture participants' perspectives on how they perceive their role within society [21].

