### Data analyses

To evaluate the effectiveness of IUDPs as complex interventions, the intervention areas will be compared with the control areas in regard to the aforementioned evaluation parameters. Regarding the IUDPs’ implementation, this includes an analysis of specific outputs, such as structural or socio-spatial changes in the neighbourhoods. In addition to the assessment of these outputs, we will focus on different outcome parameters in each city: in Bremen (I1, C1), these include Outcomes I and short-term Outcomes II; in Bochum (I2, C2), short- and long-term Outcomes II; and in Wuppertal (I3, C3), long-term Outcomes II and Impacts (Fig. 3).

Both bivariate and multivariate analyses will be conducted using established statistical procedures appropriate to the data structure. Quantitative data from the cross-sectional surveys at two time points, environmental data emerged from the different data collection formats, as well as secondary quantitative data collected at multiple time points, will be analysed using a difference-in-differences (DiD) approach [38]. Both absolute (difference-in-differences) and relative changes (ratio-of-ratios) will be assessed, and inequality effects will be examined through stratification by various social indicators [39]. From an intersectional perspective, social indicators will be selected based on the PROGRESS-Plus framework, as recommended by the Campbell and Cochrane Equity Methods Group [40]. The quantitative data analysis will be carried out using SAS (version 9.4 or higher) and R (version 4.5.1 or higher) [41].

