## Discussion

In SalusTransform, IUDPs will be evaluated for the first time in a comprehensive manner with regard to their real-world effects on residents’ health, social equity, and ecological sustainability. Drawing on diverse data sources from three different cities in Germany, we aim to gain an in-depth understanding of how IUDP measures have been implemented and what impacts they have on the living conditions of residents in the intervention areas and on the extent of environmental health inequities compared to similarly structured control areas within the same cities.

One major challenge we anticipate is ensuring participant retention across the various data collection formats. To address this, we will implement tailored strategies to facilitate participation. During the survey phases, we will attend local events in all study areas to promote the online surveys and engage directly with residents. Additionally, we will offer on-site support on selected dates to assist participants who experience difficulties completing the survey or need help reactivating their single-use access code. These support activities will be communicated through the project website, the project’s social media channels, and a general study hotline that will be available during weekdays.

Another challenge may occur when it comes to significant delays in timing and extent of the implementation of IUDP measures in Bochum and Bremen. To evaluate the process of implementation, we will collect information on reasons for any delays and potential countermeasures. Moreover, our evaluation approach focuses on the bundle of measures put into practice instead of analysing only selected single measures.

Finally, developments within the control areas that lead to the implementation of interventions comparable to an IUDP, or even to the initiation of an IUDP planning process, may pose an additional challenge. We will address this by closely monitoring developments in the control areas and applying a difference-in-differences analysis. A strength of our evaluation approach is the observation of control areas specifically identified and assigned to the IUDP area in each of the three cities. These control areas face similar challenges concerning population characteristics, infrastructure and environmental conditions, but are not located directly adjacent to the intervention areas, thus reducing the risk of spill-over effects of IUDP activities on the control areas.

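### Inequality effects are to be examined by stratification alone; the change in the social gap needs a declared area x wave x social-group contrast with its interval

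*Protocol article*

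**What the plan says.** The protocol article, Data analyses, plans DiD analyses of the two cross-sectional surveys, the environmental data and the secondary series. On scale and on equity it says: "Both absolute (difference-in-differences) and relative changes (ratio-of-ratios) will be assessed, and inequality effects will be examined through stratification by various social indicators". The strata are left open, since "social indicators will be selected based on the PROGRESS-Plus framework". The same section announces in general terms that "Both bivariate and multivariate analyses will be conducted using established statistical procedures appropriate to the data structure". It names no contrast between strata and does not say how to read the results if the two scales disagree.

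The equity aims appear in three places and are of two kinds:

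- **Outcomes** describes Impacts as fundamental changes "such as strengthened resilience or reduced inequalities". This concerns a gap.
- **Discussion** says the study will show effects "on the extent of environmental health inequities compared to similarly structured control areas within the same cities". This also concerns a gap, set against the control areas.
- **Social equity** says that "survey data will be used to analyse which social groups will be affected". This concerns the effect within each group. The section also plans to compare people's living circumstances between social groups, but not as a DiD contrast.

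**The concern.** Equity is one of the three dimensions on which the plans are evaluated. Whether an urban development plan narrowed or widened a social gap is a question about the difference between group-specific effects. Stratification delivers the components of that difference but not the difference itself with its uncertainty. A reader given one DiD per stratum is left to compare them by eye, and a large estimate in one group beside a small one in another is easily taken for an equity effect when it is within chance. With several social indicators, outcomes and cities, there are many opportunities for this.

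A second point follows from reporting two scales. When social groups start from different levels, the gap can shrink in percentage points and grow in relative terms on the same data. If the article does not say beforehand that this can happen, an unexplained conflict is hard to interpret.

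**Working it through.** The article gives no sample size, power, significance level or effect size, so there is no figure of its own to reproduce. All rates, sizes and power values below are assumptions for illustration.

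**1. What stratification gives and what the gap question needs.** For outcome levels I0, I1 (intervention area, two waves) and C0, C1 (control area), within one social group:

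- absolute: DiD = (I1 − I0) − (C1 − C0)
- relative: RoR = (I1/I0) / (C1/C0), the ratio-of-ratios

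For a disadvantaged and an advantaged group, the change in the gap is:

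- absolute: triple difference = DiD(disadvantaged) − DiD(advantaged)
- relative: RoR(disadvantaged) / RoR(advantaged)

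The point estimate of the gap change can therefore be worked out from stratified results. Its interval is not the interval of either stratum.

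**2. Reading strata side by side.** Suppose two independent strata have the same true effect, each detected with probability p. Exactly one is significant with probability 2p(1 − p):

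- p = 0.30: 2 x 0.30 x 0.70 = 0.42
- p = 0.50: 2 x 0.50 x 0.50 = 0.50
- p = 0.80: 2 x 0.80 x 0.20 = 0.32

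These figures apply only if strata are compared by significance.

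**3. The two scales on the gap.** Take poor health as the outcome, with both control groups unchanged.

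- Disadvantaged: intervention 40% to 34%, control 40% to 40%. DiD = −6 points; RoR = 0.34/0.40 = 0.85.
- Advantaged: intervention 20% to 16%, control 20% to 20%. DiD = −4 points; RoR = 0.16/0.20 = 0.80.
- Gap change: −6 − (−4) = −2 points, so the absolute gap narrows. 0.85/0.80 = 1.0625, so the relative gap widens.

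**4. Scores with an arbitrary zero.** Add a constant k to every score. The difference (I1 + k) − (I0 + k) is unchanged, but the ratio (I1 + k)/(I0 + k) moves with k. A ratio of mean scores therefore depends on the scoring convention; a ratio of proportions, rates or counts does not have this problem.

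**5. Precision of the contrast.** With two independent strata of equal size and variance, SE(triple difference) = √2 x SE(stratum DiD). At two-sided 5%, a stratum DiD with 80% power for effect d has d/SE = 1.960 + 0.842 = 2.802.

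- Other stratum's effect is 0: 2.802/√2 − 1.960 = 0.021, power 50.8%.
- Other stratum's effect is d/2: 0.5 x 2.802/√2 − 1.960 = −0.969, power 16.6%.

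With 30% prevalence, n respondents per area and wave, and two equal strata, SE(stratum DiD) = √(4 x 0.3 x 0.7/(n/2)). The detectable effect at 80% power is 2.802 x SE, multiplied by √2 for the contrast:

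| n | stratum DiD (points) | triple difference (points) |
|---|---|---|
| 200 | 25.7 | 36.3 |
| 500 | 16.2 | 23.0 |
| 1000 | 11.5 | 16.2 |

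**The case against.** The article is a condensed account. Its general sentence on multivariate analyses leaves room for an interaction term, and an analysis plan or the method paper cited for stratification may specify one; neither is at hand. That stands as a caution. It does not remove the point, because the article does state a method for inequality effects, and that method stops short of the question asked in Outcomes and the Discussion.

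Four stronger readings are tempting, and the text does not support them.

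- A reader might infer that the plan cannot estimate the gap change at all. It can: subtracting two stratum DiDs gives the point estimate. What is not named is the contrast as a target, with its interval.
- A reader might infer that inequality will be judged by which strata reach significance. The article states no significance rule, so the 42%, 50% and 32% describe a risk of side-by-side reading, not a planned practice.
- A reader might infer that using two scales is a fault, or that the additive scale must lead. Absolute and relative gaps are different quantities, and committing beforehand to both limits selective reporting. Which should lead is a trade-off.
- A reader might infer that ratios will be taken of well-being or social participation scores. The sentence on scales sets no restriction, but it does not say this, and procedures are to suit the data.

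Stratum-specific DiDs are also the direct answer to the question in Social equity about which groups are affected, so they should be kept.

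**Conclusion.** The point holds as a mismatch between the stated method and two of the stated equity aims. Stratification is the only method named for inequality effects, while the change in the gap against the control areas is a declared interest and calls for its own contrast and interval.

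The size cannot be fixed from the article. As an indication, the contrast's standard error is about 1.4 times that of a single stratum, and power falls from 80% to about 51% when only one stratum responds. Both figures assume two equal, independent strata and a two-sided 5% level. The scale conflict in the example (−2 points against a ratio of 1.0625) shows that opposite directions are possible; it does not show how often they will occur here. Nothing in this is an arithmetical error in the document.

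**What to change.** In Data analyses, replace stratification as the sole method for inequality effects with the following:

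- For each chosen social indicator, estimate the change in inequality by the area x wave x social-group contrast with its confidence interval: the triple difference on the absolute scale, and the ratio of ratio-of-ratios on the relative scale.
- Keep stratum-specific DiDs as description, to answer which groups are affected.
- Report the gap change on both scales, and state in advance that they can differ in direction when baselines differ.
- Use the ratio form only for outcomes with a meaningful zero: proportions, rates and counts.

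No new data are needed. The cost is precision and volume. The contrast is much less precise than a single-stratum DiD, with detectable differences of roughly 16 to 36 points under the sample sizes assumed above. It is also repeated over indicators, outcomes and cities, with several terms where an indicator has more than two categories. It should therefore be presented as an estimate with its interval, and an interval that includes no change should not be read as showing that the gap stayed the same.

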### Monitoring

To monitor the study, a Steering Committee (SC) and a Data Monitoring Committee (DMC) will be established. The SC will include all researchers involved in this publication and will be chaired by GB, an experienced public health researcher with expertise in interdisciplinary research on health equity and environmental justice. In regular meetings, the SC will oversee study procedures to ensure adherence to the study protocol. Key areas of focus will include recruitment processes across all data collection formats, data collection procedures, and communication with local stakeholders. The primary aim of the SC is to facilitate the smooth conduct of the study.

The DMC will consist of five members, including one data manager from the Department of Social Epidemiology at the Institute for Public Health and Nursing Research, University of Bremen. Members will possess epidemiological, statistical, and research expertise. The DMC will regularly monitor data quality and plausibility by reviewing exports from the online survey tool. Since we will not implement any intervention by ourselves, no interim analyses or auditing are planned.

## Discussion

In SalusTransform, IUDPs will be evaluated for the first time in a comprehensive manner with regard to their real-world effects on residents’ health, social equity, and ecological sustainability. Drawing on diverse data sources from three different cities in Germany, we aim to gain an in-depth understanding of how IUDP measures have been implemented and what impacts they have on the living conditions of residents in the intervention areas and on the extent of environmental health inequities compared to similarly structured control areas within the same cities.

One major challenge we anticipate is ensuring participant retention across the various data collection formats. To address this, we will implement tailored strategies to facilitate participation. During the survey phases, we will attend local events in all study areas to promote the online surveys and engage directly with residents. Additionally, we will offer on-site support on selected dates to assist participants who experience difficulties completing the survey or need help reactivating their single-use access code. These support activities will be communicated through the project website, the project’s social media channels, and a general study hotline that will be available during weekdays.

Another challenge may occur when it comes to significant delays in timing and extent of the implementation of IUDP measures in Bochum and Bremen. To evaluate the process of implementation, we will collect information on reasons for any delays and potential countermeasures. Moreover, our evaluation approach focuses on the bundle of measures put into practice instead of analysing only selected single measures.

Finally, developments within the control areas that lead to the implementation of interventions comparable to an IUDP, or even to the initiation of an IUDP planning process, may pose an additional challenge. We will address this by closely monitoring developments in the control areas and applying a difference-in-differences analysis. A strength of our evaluation approach is the observation of control areas specifically identified and assigned to the IUDP area in each of the three cities. These control areas face similar challenges concerning population characteristics, infrastructure and environmental conditions, but are not located directly adjacent to the intervention areas, thus reducing the risk of spill-over effects of IUDP activities on the control areas.

The results of this study will be presented to academic, municipal, and public audiences. During the project period, city-specific information tailored to residents, practitioners, and local policy representatives will be disseminated via the project website and local events such as neighbourhood or community meetings. Final dissemination events in each city will present key results and discuss their implications for health-promoting, socially equitable, and environmentally sustainable urban development. Continuous collaboration with municipal stakeholders will support transdisciplinary exchange and contribute to the institutionalisation of evaluation practices for urban renewal measures. Scientific dissemination will include publications in peer-reviewed journals and presentations at national and international conferences.

In the longer term, the project seeks to transfer its evaluation approach to other municipalities through established research and practice networks. Furthermore, results and methodological insights will be integrated into teaching and professional training at the three participating research institutes.

This study was prospectively registered with the German Clinical Trials Register (DRKS00036042) on May 28th, 2025.

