**Methods:**

We will compare three IUDP intervention areas with three control areas in the respective cities using a mixed-methods design. Quantitative and qualitative data will be collected to assess both process and outcome quality of the IUDPs. Primary data collections include resident surveys and focus groups, qualitative interviews with stakeholders, as well as environmental and infrastructural assessments, including air-quality measurements, site visits, and observations related to active mobility and urban green spaces. Secondary data on population structure, aggregated health indicators, and local implementation processes will be provided by the municipalities. Analyses will follow a difference-in-differences approach to identify changes attributable to IUDP implementation while accounting for similar developments in the control areas.

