## Methods

### Study setting

This study will evaluate the impact and process quality of IUDPs in three urban areas in Germany. The intervention areas are the districts of Blumenthal (I1) in the city of Bremen, federal state of Bremen in northern Germany, Wattenscheid-Mitte (I2) in Bochum and Mirke (I3) in Wuppertal, both cities located in the federal state of North Rhine-Westphalia in the western part of Germany. In each city, a further district will serve as control area in which no IUDP will be implemented. These control areas are Bremen Kirchhuchting (C1), Bochum Hofstede (C2) and Wuppertal Rott (C3). For the localisation of all six study areas within Germany and the respective cities, see Fig. 1.

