#### Surveys of the residents

We will conduct two surveys in the study areas, one in the first and the other in the third year of the project. The surveys will target residents aged 18 years and older living within the defined study areas. In Bremen and Wuppertal, all residents will receive a personal access code enabling them to complete the survey online. In Wattenscheid-Mitte, due to the substantially larger population, a random sample of residents will be invited to participate, with the number of invitations adjusted to achieve a sample size comparable to the other intervention areas. The survey will be implemented on LimeSurvey, an open-source online survey tool [19]. The survey will include a set of validated questionnaires: Warwick Edinburgh mental well-being scale [20], Short Scale Measuring Perceived Social Participation [21], Oslo-3-Items-Social-Support Scale [22], self-efficacy short scale [23], and Abbreviated Place Attachment Scale (APAS) [24]. We will also use items on general mental and physical health status from the German Federal Health Reporting surveys, provided by the Robert Koch Institute (RKI) [25]. Furthermore, we will collect information about the participants’ living and housing situation, their subjective assessment of their living environment concerning (1) traffic infrastructure, (2) impairments due to noise, air pollution, and other environmental threads, (3) the proximity and accessibility of public green spaces, as well as their perceived impact on and involvement in urban planning decisions affecting their living environment. We will provide translations of the questionnaire in the most common languages of the study areas.

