### Secondary data sources

In addition to primary data, we will collect secondary data from various sources provided by the respective city authorities. These data will include information on the population structure of the study areas (e.g. number of inhabitants, age distribution, proportion of residents with a migration background, unemployment rates, and other sociodemographic indicators), as well as aggregated health and environmental data. Health data will include indicators such as life expectancy, results from school entry examinations, and other aggregated public health statistics. Environmental data will include information on air and noise pollution, heat exposure, and the availability and quality of green spaces.

For the intervention areas, we will also gather detailed information on the IUDPs’ implementation processes from the responsible authorities, including data on expenditures, participation rates, and the use of specific interventions such as counselling services or small subsidy programmes for private homeowners. Additionally, we will document any delays in the implementation and their underlying causes. To ensure a longitudinal perspective, secondary data will be collected retrospectively for a period of ten years prior to the start of the respective IUDP and continuously throughout the project duration.

In the control areas, we will assess whether any interventions are planned or implemented that target similar dimensions as the IUDPs but have not been formally developed or approved as such. Close cooperation with local authorities and the wider network of practitioners in the study areas, established during the project conception phase, will ensure comprehensive and reliable access to these data sources.

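### Difference-in-differences is named as a remedy for IUDP-like measures in a control area, but it subtracts their effect instead of correcting for it

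*Protocol article*

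**What the plan says.** The Study setting section defines the counterfactual: "In each city, a further district will serve as control area in which no IUDP will be implemented". Each of the three cities therefore has one intervention area and one control area.

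The Discussion then lists as a challenge "developments within the control areas that lead to the implementation of interventions comparable to an IUDP", and extends it to the start of IUDP planning there. Its answer has two parts: "We will address this by closely monitoring developments in the control areas and applying a difference-in-differences analysis".

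The Secondary data sources section supports the monitoring part. In the control areas, "we will assess whether any interventions are planned or implemented that target similar dimensions as the IUDPs". It does not link that information to the estimate.

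The abstract uses similar language for the analysis: "Analyses will follow a difference-in-differences approach to identify changes attributable to IUDP implementation while accounting for similar developments in the control areas". The Data analyses section names two effect scales: "Both absolute (difference-in-differences) and relative changes (ratio-of-ratios) will be assessed". The resident surveys are held twice, "one in the first and the other in the third year of the project".

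**The concern.** DiD protects against change that both areas would have undergone anyway. A measure that begins in the control area is not shared change. Its effect becomes part of the control-area change, and DiD subtracts that change from the intervention area's. The Discussion therefore credits the method with a property it lacks, in the very scenario where the method passes the bias on.

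What is at stake is the reading of a small or null result. With one control per city, a treated control affects that city's whole comparison. A reader who has been told that DiD deals with the problem could take an attenuated estimate as evidence that the IUDP did little.

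**Working it through.** **Is there a figure to reproduce?** No. The article states no effect size and no expected level of control-area activity. The numbers below are illustrations on assumed inputs.

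**Notation.** T is the change common to both areas. d_I and d_C are the effects that arise between the two time points in the intervention and control area.

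**Step 1: expected value of DiD.**

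E[DiD] = (T + d_I) − (T + d_C) = d_I − d_C.

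T cancels and d_C does not.

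**Step 2: control gains a fraction f of the intervention effect.** Put d_C = f·d_I, with the same direction assumed. Then E[DiD] = (1 − f)·d_I. With d_I = 1 and f = 0.5:

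- T = 0: (1 + 0) − (0.5 + 0) = 0.50
- T = 0.7: (1 + 0.7) − (0.5 + 0.7) = 0.50

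The common trend makes no difference; the contamination remains.

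**Step 3: range of f on both planned scales.** For the ratio-of-ratios, assume a true ratio of 1.20 and a control that gains the fraction f on the log scale. The expected ratio is 1.20^(1 − f).

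| f (assumed) | DiD, share of true effect | Ratio-of-ratios (true value 1.20) |
|---|---|---|
| 0 | 1.00 | 1.20 |
| 0.25 | 0.75 | 1.147 |
| 0.5 | 0.50 | 1.095 |
| 1 | 0.00 | 1.00 |

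**Step 4: one city or all three.** The Data analyses section assigns different outcome levels to each city, so the city-level figures in Step 3 are the relevant ones. If the three cities were combined with equal weights (an assumption) and one control were affected, the share of the effect retained would be (1 + 1 + (1 − f))/3. That is 0.917, 0.833 and 0.667 for f = 0.25, 0.5 and 1.

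**Step 5: how large could f be?** The section describing the study areas and IUDPs says that development and implementation often take six years or more. The surveys fall in project years 1 and 3. A control area that only starts planning within that window may deliver few measures before the second survey, so f by that route could be close to 0. Comparable measures carried out without a formal plan could act sooner. The protocol does not allow f to be estimated for either route.

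**The case against.** **Monitoring is half of the stated remedy.** This stands. Monitoring is backed by the Secondary data sources section and would show that a control has been treated, so the estimate could be read with that in mind. It would be wrong to say that the plan relies on DiD alone. Detection still does not change the estimate, and DiD is the only analytic step named.

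**Analysis rules belong in an analysis plan that is not shown.** This stands as far as missing detail goes, and the absence of a sensitivity analysis from a condensed article is not the point made here. The point is a statement the article does make. A later analysis plan could add rules, but the published claim about DiD would remain incorrect.

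**Subtracting non-IUDP measures may be intended.** If the comparison is with ordinary municipal development, routine control-area measures belong to the comparator. The abstract can be read that way. But the Discussion treats such measures as a challenge, so the comparator is left ambiguous. An IUDP taking effect in a control area would contaminate the comparison on either reading.

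**Stronger readings.** A reader might infer that contamination could reverse the sign of an estimate. With f between 0 and 1, (1 − f)·d_I does not change sign. Reversal needs a control gain larger than the remaining intervention gain, for example 0.5 − 0.75 = −0.25. The documents give no basis for such values. The IUDPs in Bochum and Wuppertal did start years before the surveys, but nothing states how much effect remains, and Bochum entered a second funding phase in early 2025. A reader might also infer that a control starting its own IUDP would wipe out the effect. That needs f near 1, which the timing in Step 5 makes unlikely when planning begins during the study.

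**Conclusion.** The claim that DiD, together with monitoring, addresses IUDP-like activity in a control area is incorrect as regards DiD. If such measures act in the same direction as the IUDP and take effect between the two time points, the city's estimate is attenuated to d_I − d_C: half the effect if the control gains half of it, three quarters if it gains a quarter. These fractions are assumptions, and the true size is unknown. The bias is conditional. It arises only if a control area is in fact treated, and it may be small if only planning begins.

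The authors disclose the threat and plan to watch for it, so the point ranks below a must-fix. It still deserves correction because it determines what a null or small result can be taken to mean.

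**What to change.** 1. In the Discussion, remove DiD as a remedy for control-area contamination. Keep monitoring, described as a means of detection and interpretation. In the abstract, make clear that accounting for similar developments refers to common trends only.
2. State the comparator: IUDP versus usual municipal development without an IUDP. Routine non-IUDP measures then belong to the comparison by design.
3. Record IUDP-like measures in intervention and control areas with dates and on the same domains, using the monitoring already planned.
4. Pre-specify a sensitivity analysis, triggered if a control area starts an IUDP or a comparable bundle. It leaves out the affected city pair or, for the secondary series, the affected period. State that a null or small estimate in that city will be read as possibly attenuated.

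Two other remedies are better avoided. Dividing the estimate by (1 − f) would need an effect fraction that an activity record does not supply, would grow without bound as f approaches 1, and would remove routine measures that item 2 places in the comparator. Replacing an affected control with other districts would give up the chosen comparison for less similar areas. In Table 1, unemployment is 22.0% in the Bremen intervention area, 19.0% in its control and 12.6% in the city as a whole.

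**Cost.** A few sentences and a structured form for monitoring that is already planned. The downside is lower precision in the sensitivity analysis if contamination occurs. Leaving out an affected pair also leaves that city without an uncontaminated survey comparison. The change should be made before control-area developments and results are known.
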